#### Objectives and expected outcomes of AP -JD Program

In this demonstration project (Asia Pacific JADE and DIAMOND Program, AP-JD in short) supported by ADF, patients will be recruited from different sites across Asia, with each site recruiting at least 600 type 2 diabetic patients. After explanation by trained doctors and nurses, and with written informed consent, patients will be randomized to either the JADE (n=300, structured care) or DIAMOND (n=300, usual care) group. All patients will undergo a comprehensive assessment (CA) at baseline and yearly thereafter. Patients in the JADE group will be further managed by a doctor-nurse-HCA team according to a protocol based on risk stratification with predefined follow up (FU) schedules together with shared information and decision support (i.e. structured collaborative care). The DIAMOND protocol involves only baseline and yearly CA without predefined FU schedules or feedback of information between CA visits (i.e. usual care). The primary composite endpoint is all-diabetes related clinical endpoints. The secondary composite endpoint is attainment of treatment goals and/or control of risk factors. The tertiary changes are behavioral changes, psychological well being and quality of life.

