2) Proportions of patients with improved control of risk factors defined as:

- a) 2 or more of the ‘ABC’ targets:
  - i) HbA1c < 7%
  - ii) BP < 130/80 mmHg
  - iii) LDL-C < 2.6 mmol/L
- b) and/or
- c) 2 of the following changes in risk factor control:
  - i) at least 0.5% reduction in HbA1c
  - ii) at least 5 mmHg reduction in systolic BP
  - iii) at least 0.5 mmol/L reduction in LDL-C
  - iv) at least 3% reduction in body weight

Composite tertiary endpoint

- 3) Quality of life (ED-5Q)
- 4) Frequency of hypoglycaemia (in the last 3 months) as recorded in the JADE CA form
- 5) Behavioral changes in last 3 months as recorded in the JADE CA form
  - a) Frequency of Self Blood Glucose Monitoring
  - b) Adherence to balanced eating
  - c) Adherence to regular exercise
- 6) CQ4 for compliance
- 7) PHQ-9 for depression
- 8) Hospitalization days and cost-effectiveness analysis
- 9) Additional questionnaires are available for interested investigators to assess other psychological parameters (self efficacy, diabetes related stress, perception of happiness, personal habits) and self-care activities to explore reasons which may explain differences in outcomes between the 2 groups (see appendix).

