In a multicentre randomized study involving Chinese type 2 diabetic patients with chronic kidney disease, 61% of patients receiving team-based structured care achieved 3 or more treatment goals (HbA1c<7%, LDL-C<2.6 mmol/l, BP<130/80 mmHg, triglyceride<2 mmol/l and persistence with ACE inhibitor or AII receptor blockers) compared to 28% in the usual care group, i.e. 2-fold increase. Patients who attained 3 or more treatment targets had 50% risk reduction of dialysis or ESRD at 2 year (29).

Based on these observations, we assume that the rate of attaining at least 2 'ABC' goals will increase by 2-fold compared to 50% in the usual care group and assuming 20% attrition rate, we estimate that 295-1814 patients will give the study sufficient power depending on the baseline rate of attaining 2ABC goals. In the first year analysis of the Asia Pacific JADE Program, 12-36% of patients attained at least 2 treatment goals with an average value of 30%.

|                                   | Total
(3687) | HK
(832) | India
(788) | Korea
(295) | Ph
(1186) | Sing
(256) | TW
(55)  | Thai
(275) |
|-----------------------------------|-----------------|-------------|----------------|----------------|--------------|---------------|-------------|---------------|
| HbA 1c <7%             | 35.3            | 61.8        | 13.8           | 40.7           | 31.3         | 35.2          | 25.5        | 29.8          |
| BP<130/80
mmHg                 | 32.3            | 45.6        | 26.0           | 38.3           | 27.2         | 12.9          | 34.6        | 42.9          |
| LDL-C<2.6
mmol/L               | 34.0            | 39.2        | 44.8           | 33.6           | 20.5         | 29.7          | 20.0        | 52.7          |
| No target
achieved     | 32.6     | 14.3 | 38.3    | 28.1    | 42.2  | 42.8   | 40.0 | 23.3   |
| Any 1 target
achieved          | 38.7            | 37.1        | 40.6           | 36.6           | 39.2         | 37.9          | 43.6        | 37.5          |
| Any 2 targets
achieved         | 23.4            | 36.3        | 19.2           | 29.8           | 16.2         | 15.2          | 12.7        | 29.8          |
| All 3 targets
achieved | 5.4      | 12.3 | 1.9     | 5.4     | 2.5   | 3.1    | 3.6  | 9.5    |

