We also estimate the sample size needed to confirm the benefits of team-based care on controlling multiple risk factors. Apart from LDL-C goal, which can readily be achieved by initiating patients on statin therapy and thus requires a larger number to detect the small difference between the usual care and structured care groups, we estimate that 300-600 patients will be needed to confirm the superior effects of structured care. Given the expected heterogeneity in clinic settings, patient profiles and health care systems amongst different sites, a sample size of 600 patients will give each site sufficient power to confirm the superior effects of team-based structured care within their own clinic setting.

|                                         |      |      |      |
|-----------------------------------------|------|------|------|
| % of patients at 2 ABC goals in JADE-AP | 0.36 | 0.3  | 0.12 |
| SC (increased by 2-fold)                | 0.72 | 0.6  | 0.24 |
| UC (increased by 50%)                   | 0.54 | 0.45 | 0.18 |
| absolute difference                     | 0.18 | 0.15 | 0.06 |
| 80% at 0.05 alpha each group            | 123  | 186  | 756  |
| total sample size                       | 246  | 372  | 1512 |
| assuming 20% attrition rate             | 295  | 446  | 1814 |
| number needed to treat                  | 6    | 7    | 17   |

| Risk factors
units                          | A1c
% | A1c
% | SBP
mmHg | SBP
mmHg | LDL-C
mmol/l | LDL-C
mmol/l | BW   | BW    |
|------------------------------------------------|----------|----------|-------------|-------------|-----------------|-----------------|------|-------|
| reduction in risk factors compared to baseline | 0.5      | 1        | 5           | 10          | 0.5             | 1               | 0.03 | 0.05  |
| proportion of patients in SC                   | 0.77     | 0.61     | 0.46        | 0.35        | 0.32            | 0.16            | 0.16 | 0.087 |
| proportion of patients in UC                   | 0.6      | 0.44     | 0.29        | 0.18        | 0.26            | 0.09            | 0.06 | 0.026 |
| absolute difference                            | 0.17     | 0.17     | 0.17        | 0.17        | 0.06            | 0.07            | 0.1  | 0.061 |
| 80% at 0.05 alpha each group                   | 128      | 146      | 138         | 117         | 930             | 378             | 172  | 256   |

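### The secondary endpoint is labelled improved control, but its first limb is a follow-up status that about 29% of patients in the planning data already meet, so unchanged patients would be reported as improved

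*Protocol*

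**What the plan says.** The operative definition is in the protocol under Outcome Measures, Composite secondary endpoint. It is headed "Proportions of patients with improved control of risk factors defined as" and has two limbs:

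- Limb (a): "2 or more of the ‘ABC’ targets", that is, HbA1c, blood pressure and LDL-C below fixed cut-offs.
- Limb (c): "2 of the following changes in risk factor control", chosen from falls in HbA1c, systolic pressure, LDL-C and body weight.

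Item (b) in the list is only the connective and/or, so meeting either limb is enough. The eligibility criteria do not exclude patients already at two or more targets.

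Two other places describe the same endpoint differently. The executive summary states: "The secondary composite endpoint is attainment of treatment goals and/or control of risk factors". The sample-size section (Secondary composite outcome) reports from the programme's first year that "12-36% of patients attained at least 2 treatment goals with an average value of 30" per cent, and enters the percentage "of patients at 2 ABC goals in JADE-AP" as the starting rate for a calculation of how many patients attain the targets.

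**The concern.** Limb (a) does not look at where the patient started. A patient at two targets on the day of randomisation and at the same two targets two years later meets it. So does a patient who started at three and lost one. Both would be counted under a heading that says control has improved. Only limb (c) measures change, and it is not required.

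What is at stake is the interpretation of the headline proportions. A published percentage improved would mix newly gained control, maintained control and a little lost control. Its level would depend partly on starting attainment, which differs about threefold between countries in the protocol's own table. That matters more because the sample-size section intends each site of 600 to draw its own conclusion. Baseline attainment is also known for everyone from the first comprehensive assessment, so leaving it out of the comparison gives up some precision at no saving.

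**Working it through.** **1. The plan's own figure.** For 30% starting attainment, the sample-size table assumes 0.60 (structured care, doubled) against 0.45 (usual care, raised by half). With a two-sided 0.05 test, 80% power and a continuity-corrected two-proportion formula, the stated 186 per group is reproduced exactly, as are 123 and 756 in the neighbouring columns. The planning quantity is therefore attainment of two or more targets, not improvement and not the composite of both limbs.

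**2. Share already meeting limb (a).** From the programme table (N = 3687), exactly two targets plus all three:

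| | Exactly 2 | All 3 | At least 2 |
|---|---|---|---|
| Total | 23.4 | 5.4 | 28.8 |
| Hong Kong | 36.3 | 12.3 | 48.6 |
| Thailand | 29.8 | 9.5 | 39.3 |
| Korea | 29.8 | 5.4 | 35.2 |
| India | 19.2 | 1.9 | 21.1 |
| Philippines | 16.2 | 2.5 | 18.7 |
| Singapore | 15.2 | 3.1 | 18.3 |
| Taiwan | 12.7 | 3.6 | 16.3 |

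At 28.8%, about 0.288 × 300 = 86 patients per arm at a site would satisfy limb (a) on the day of randomisation. The text's average of 30% agrees with the total. Its range of 12–36% matches the exactly-two column (12.7 to 36.3), not the at-least-two column. The pilot in high-risk patients started at 15% (structured care) and 20% (usual care).

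**3. The three-to-two route.** Only patients starting at all three targets can take it: at most 5.4% overall and 12.3% in Hong Kong.

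**4. Share of limb (a) attainers who were at target at entry.** Let r be the fraction of baseline attainers still at two or more targets at follow-up. The protocol gives no value. I assume 0.6 to 0.8, equal in both arms. With 30% at entry:

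- Usual care: 0.30r / 0.45 = 0.18/0.45 to 0.24/0.45 = 40% to 53%.
- Structured care: 0.30r / 0.60 = 0.18/0.60 to 0.24/0.60 = 30% to 40%.

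**5. Adding limb (c).** The pilot's usual-care proportions for the four changes are 0.60, 0.29, 0.26 and 0.06. If they are independent:

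- P(none) = 0.40 × 0.71 × 0.74 × 0.94 = 0.198
- P(exactly one) = 0.198 × (1.500 + 0.408 + 0.351 + 0.064) = 0.459
- P(two or more) = 1 − 0.198 − 0.459 = 0.343

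If limb (c) is also independent of limb (a), the usual-care composite rate is 1 − 0.55 × 0.657 = 0.639. Patients who keep limb (a) from baseline are then 0.18/0.639 to 0.24/0.639 = 28% to 38% of usual-care successes. Independence is unlikely to hold exactly and the pilot patients were high-risk, so this only illustrates that limb (c) lowers the share.

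**6. Precision.** For limb (a) in usual care, the attainment rate among patients below two targets at entry is (0.45 − 0.30r)/0.70, which is 0.386 at r = 0.6 and 0.300 at r = 0.8. The variance explained by baseline status is (r − that rate)² × 0.30 × 0.70 / (0.45 × 0.55):

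- r = 0.6: 0.214² × 0.21/0.2475 = 0.04
- r = 0.8: 0.500² × 0.21/0.2475 = 0.21

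The same formula in structured care, with 0.60 × 0.40 = 0.24 as denominator, gives 0 at r = 0.6 (both rates are 0.60) and (0.800 − 0.514)² × 0.21/0.24 = 0.07 at r = 0.8. The gain is real but may be small.

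**The case against.** The strongest reply is that the trial compares arms. Randomisation is 1:1 with separate codes for each site, so baseline attainers, and the differences between countries, fall equally on both arms in expectation. The hypothesis is better control than under usual care, and keeping a patient at target is part of control. A difference in the proportion at target tests that directly. All of this stands.

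A reader might therefore infer too much in three ways:

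- **That the between-arm test is biased or its error rate wrong.** Nothing in the protocol supports this. Chance imbalance is already allowed for by the test. At 300 per arm and 28.8%, the standard error of the baseline difference is √(2 × 0.288 × 0.712/300) = 3.7 percentage points. The pilot's 15% against 20%, in 240 patients, is about one standard error (4.9 points if split equally).
- **That the endpoint is largely a baseline characteristic or fails to address the hypothesis.** Even on limb (a) alone, baseline status explains only about 4–21% of the usual-care variance, and limb (c) dilutes it further.
- **That falling from three targets to two is a main route to success.** It is open to at most 5.4% of patients.

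It is also fair that the 28.8% comes from earlier programme data rather than trial patients, and that covariates may be fixed in an analysis plan that is not shown. The Data Analysis section lists chi-squared tests and analysis of covariance, to be used as suits. So adjustment is put forward here as a better method, not as an omission. None of this removes the mismatch between the endpoint's label and its definition, which sits in the protocol itself.

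**Conclusion.** The point holds as a fault of definition and labelling. Limb (a) alone qualifies a patient as improved. In the data the protocol plans on, 28.8% of patients (16.3–48.6% by country; 15–20% in the pilot) would qualify without any change. The executive summary and the sample-size calculation treat the same endpoint as attainment, so the protocol disagrees with itself.

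The size depends on an assumed retention of 60–80%, equal in both arms, and on 30% starting attainment. On limb (a) alone, patients at target at entry are 40–53% of usual-care and 30–40% of structured-care attainers. With limb (c) added under independence, the usual-care share is about 28–38%. No test, error rate or sample size is shown to be wrong. The loss is in the meaning of the reported proportions and, to a modest and uncertain degree, in precision.

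**What to change.** In the Composite secondary endpoint definition, name limb (a) attainment of two or more ABC targets, in line with the executive summary. Keep the word improved for limb (c) and for new attainment among patients below two targets at baseline. Report new attainment as a supportive analysis, and show maintenance among baseline attainers separately.

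Compare the arms on the secondary endpoint by logistic regression, with baseline number of ABC targets (0, 1, 2, 3) and site as covariates.

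The cost is wording, one extra table and covariates already collected. The supportive new-attainment analysis uses only about 70% of patients. It need not be underpowered. At 30% starting attainment and the protocol's rates, with equal retention of 60–100% in both arms, the same continuity-corrected formula needs 119–135 enrolled per arm before attrition, against the stated 186. That figure assumes the whole treatment effect falls on patients not yet at target.

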## STUDY PROTOCOL

### Infrastructure, logistics and manpower

The doctor will identify a dedicated space, however small, which can accommodate a couch and office equipment to enable the nurse and HCA to perform clinical assessments, interview patients, and manage a database. The doctor will provide simple equipment and make necessary arrangements to help the nurse complete the CA including eye and feet examination, blood and urine tests. The doctor will emphasize to patient the important role of a nurse in assisting doctors to provide continuous and quality care. Patients enrolled in the program will be given easy access to attend these assessment and education sessions (e.g. pre-booked appointments) to reduce waiting time and default rate.

### Randomization

Computer-generated codes numbered 1 to 600 with assignment to either JADE or DIAMOND group will be prepared by ADF for each site. Three sets of envelopes with equal assignment to JADE or DIAMOND Group will be given to the study site at regular time intervals depending on rate of recruitment. The randomization procedures are as follows:

- 1) The doctor or nurse will explain to eligible patients regarding the international recommendation on performing regular CA to detect silent risk factors and complications.
- 2) They will also explain to patients the need to assess cost-effectiveness of using a team to implement structured care by comparing the latter with usual care.
- 3) After the patient has signed the consent, a staff not participating in the study will open the envelope containing the randomization group and sign and date the envelope.
- 4) The signed envelope will be kept by the nurse in a secure place for audit purpose.
- 5) The nurse will explain to patient whether they have been randomized to JADE or DIAMOND and the assessment will proceed accordingly.
- 6) The nurse will fax the randomization form to the ADF office and keep a log of randomized patients and record status including study completion, premature discontinuation, consent withdrawal or lost to follow up.
- 7) The doctor or nurse will contact the ADF to obtain the user code to enrol the patient in either the JADE or DIAMOND portal and obtain a patient identification number (ID).

[figure not shown]

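### The arm is opened and disclosed at the site before the coordinating centre is told of the patient; registering the patient first would cheaply close a gap for selective omission

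*Protocol*

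**What the plan says.** The Randomization section of the Protocol starts from a central list: "Computer-generated codes numbered 1 to 600 with assignment to either JADE or DIAMOND group will be prepared by ADF for each site". The allocations then go to the clinics: "Three sets of envelopes with equal assignment to JADE or DIAMOND Group will be given to the study site at regular time intervals". Seven numbered steps follow. The ones that matter here are:

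- Step 3: "After the patient has signed the consent, a staff not participating in the study will open the envelope containing the randomization group", and that person signs and dates it.
- Step 4: "The signed envelope will be kept by the nurse in a secure place for audit purpose".
- Step 5: "The nurse will explain to patient whether they have been randomized to JADE or DIAMOND and the assessment will proceed accordingly".
- Step 6: "The nurse will fax the randomization form to the ADF office and keep a log of randomized patients". The log also records each patient's status, including withdrawal of consent and loss to follow-up.
- Step 7: "The doctor or nurse will contact the ADF to obtain the user code to enrol the patient in either the JADE or DIAMOND portal". The patient ID is obtained at the same contact.

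Three other sections bear on this. Study Design places the baseline comprehensive assessment after randomisation. Data Analysis defines the primary analysis set as randomised patients with at least one visit or phone contact after randomisation. Site Visits and Event Adjudication provides for periodic visits by the ADF project team to check data integrity.

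**The concern.** The trial is open, and the doctor and nurse who recruit also deliver the JADE intervention. In the listed order, the site and the patient know the arm before anything about that patient has reached ADF. If a patient loses interest on hearing the arm, or the team would rather not proceed, the form may simply not be sent. ADF would then hold no earlier record to show that a randomised patient is missing.

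Two features of the plan make such an omission harder to see. The baseline assessment comes after disclosure, so no baseline data need exist for the patient. Eligibility depends partly on willingness to return for follow-up, so a patient lost at this moment could be regarded as never eligible.

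At stake is the comparability of the arms. If omission after allocation depends on both arm and prognosis, the groups analysed are no longer those that randomisation produced, and an analysis of the reported patients cannot restore them.

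**Working it through.** The main check is of sequence, since the Protocol gives no figure on this point.

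**Order of events**

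| Step | Event | Arm known at site? | ADF aware of patient? |
|---|---|---|---|
| 3 | Consent already signed; outside staff member opens envelope | Yes, from here | No |
| 4 | Nurse stores the signed envelope | Yes | No |
| 5 | Patient told the arm | Yes | No |
| 6 | Form faxed, log entry made | Yes | Yes, first notice |
| 7 | User code and patient ID obtained | Yes | Yes |

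The first central notice is the fax at step 6; the ID follows at step 7. Nothing listed before step 3 records the patient at ADF, and no step has ADF compare envelope numbers with forms or IDs.

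**How much could omission matter? An illustration**

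Inputs:
- Very-high-risk patients: 7% a year (Sample Size Calculation, Primary composite outcome), so 2 × 7% = 14% over two years, doubling the annual rate as the Protocol's own tables do.
- Average two-year risk p: 6%, assumed.
- Share f of one arm that is opened but never reported: 5%, assumed. The documents give no value.
- No true treatment effect.

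Risk in the depleted arm = (p − f × 0.14) / (1 − f).

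With p = 0.06 and f = 0.05: (0.06 − 0.007) / 0.95 = 0.053 / 0.95 = 0.0558.

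- Omitted from JADE: 0.0558 / 0.06 = 0.93.
- Omitted from DIAMOND: 0.06 / 0.0558 = 1.08.

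Range over the assumed values (4% and 10% are other two-year usual-care rates in the Protocol's sample size tables):

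| p | f | Risk in depleted arm | Ratio if omitted from JADE | Ratio if omitted from DIAMOND |
|---|---|---|---|---|
| 6% | 2% | 0.0572 / 0.98 = 0.0584 | 0.97 | 1.03 |
| 6% | 5% | 0.053 / 0.95 = 0.0558 | 0.93 | 1.08 |
| 6% | 10% | 0.046 / 0.90 = 0.0511 | 0.85 | 1.17 |
| 4% | 5% | 0.033 / 0.95 = 0.0347 | 0.87 | 1.15 |
| 10% | 5% | 0.093 / 0.95 = 0.0979 | 0.98 | 1.02 |

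For comparison, the sample size rests on a hazard ratio of 0.8.

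**Are the balanced envelope sets a separate problem?** Assume three sets of 200, each 100:100 in simple random order. A simulation gives about 2 allocations at the end of each set that are certain in advance: 3 × 2 / 600 = 1%. Predictability from the balanced sets is therefore minor.

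**The case against.** The strongest reply is that the procedure already contains real safeguards. ADF generates and numbers the codes. Consent is signed before opening. The opener is outside the study and leaves a signature and date. The used envelope is kept for audit, the log covers randomised patients and has a category for withdrawn consent, and ADF makes periodic visits at which gaps in the numbering could be found. Leaving out a patient whose envelope had been opened would breach the procedure. The primary analysis is also defined on randomised patients, not on those entered in a portal, so a logged patient without a portal ID is not excluded for that reason. All of this stands, and it limits the point to opened allocations that are not reported.

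A reader might go further and infer that concealment is unprotected. The text does not support that. Omission after opening is a loss after randomisation, not foreknowledge before enrolment. The Protocol does not say that the study team holds the unopened envelopes; step 4 gives the nurse only the used ones. The text is silent on sealing and on use in number order, but a figure that follows the steps is not shown, so that silence is weak evidence.

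A reader might also model patients being exchanged between arms, which moves the ratio further than omission does. An exchange needs foreknowledge of the allocation or a swap past the outside opener, and nothing in the documents shows either.

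The direction is open too. Patients who leave on hearing that they will have usual care deplete DIAMOND. If they were at high risk, the bias would run against JADE. The formal JADE risk level normally comes from the assessment done after randomisation, although a clinician may know the history beforehand.

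The safeguards leave one gap: they depend on someone at the site reporting the opened envelope, or on a later check that the Protocol does not require.

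**Conclusion.** The point holds as a cheap improvement. It is not a failure of allocation concealment. The stated order discloses the arm before ADF has any record of the patient, and no reconciliation of envelope numbers is required, so selective omission after randomisation is possible despite the partial safeguards.

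Neither the size nor the direction of any bias can be known from the documents. Under the assumptions above (6% average two-year risk, 5% of one arm omitted, all very high risk, no true effect), the apparent ratio is about 0.93 or about 1.08, depending on which arm loses the patients. Across the assumed values shown it runs from 0.85 to 0.98 for losses from JADE, and from 1.02 to 1.17 for losses from DIAMOND. These figures show that small selective losses are not negligible beside a planned hazard ratio of 0.8. They do not predict that such losses will occur.

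**What to change.** Reorder the steps under Randomization:

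1. After consent and the eligibility check, the site registers the patient with ADF and receives the patient ID and the next code number.
2. Only then does the outside staff member open, sign and date that envelope, or ADF releases the allocation itself.
3. The arm is then disclosed to the patient and the portal user code issued.

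Add two rules. Every ID issued counts as a randomised patient, so anyone later left out of the primary analysis set for want of a visit or contact is visible and can be counted by arm. ADF reconciles every envelope number against the IDs issued.

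No extra staff are needed for enrolment, because sites already contact ADF for each patient and the contact only moves earlier. Reconciliation is a modest clerical task for ADF. The one real downside is that enrolment then depends on ADF or a web form being reachable at that moment.
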